## Methods/Design

### Study design

The Support strategies for Whole food diets, Intermittent Fasting and Training (SWIFT) study is a 5-arm randomised controlled trial testing the effectiveness of different support strategies for encouraging appropriate behaviour change for effective weight management. Participants will be randomised to one of the five groups for a 12-month intervention, with further follow-up at 24 months (Fig. 1) to determine whether any changes have been sustained. The primary analysis will be modified intention to treat (using all available data) and will focus on the outcomes resulting from the different support strategies (RCT analysis).

**Fig. 1 Fig1:**
[figure not shown]
Overview of the study design including choice of diet/exercise plan and randomisation to support strategy

The trial has been approved by the University of Otago Human Ethics Committee (H14/024) and is registered with the Australian New Zealand Clinical Trials Registry ACTRN12615000010594. Written informed consent will be obtained from all participants before randomisation.

### Participants and recruitment

Recruitment will occur by advertisement (flyers, newspapers, email distribution lists) and word of mouth and interested people will be directed to complete an online screening questionnaire. They will be deemed eligible to attend a screening appointment if they indicate that they are at least 18 years of age, their self-reported body mass index (BMI) is greater than 27, they have internet access, they intend to remain in the local area for the duration of the 2-year intervention, and if female, they are not planning to become pregnant in next two years nor are currently breastfeeding, and have no history of cardiovascular or other serious medical conditions. Presence of symptoms suggesting undiagnosed heart disease and current medication use will be reviewed by medical staff. Further exclusions will occur for diabetes mellitus type 1 and 2, endocrine disorders, systemic inflammatory diseases and musculoskeletal disorders preventing exercise. People with stage one hypertension, dysglycaemia and mild controlled asthma will be potentially eligible.

### Screening appointment

Potentially eligible participants will attend a screening session following a 12-hour overnight fast. Duplicate measurements of height, weight, and systolic/diastolic blood pressure will be undertaken using standard techniques and venepuncture blood samples will be collected by a registered nurse. Participants will complete a comprehensive baseline questionnaire, and be instructed on how to complete a 3-day weighed diet record over the next week. Participants will also wear an Actigraph accelerometer for 7 days and nights to assess physical activity and sleep during the same time period. Further exclusion criteria will be applied at this point: measured BMI less than 27, fasting blood glucose greater than 7 mmol/L (if randomised to hunger training, fasting blood sugars consistently above 7 mmol/L would result in difficulties for the participant to adhere to hunger training guidelines), systolic BP greater than 160 mmHg or diastolic BP greater than 100 mmHg (because they require medical management for their hypertension). All participants will also undergo a dual-energy x-ray absorptiometry (DXA) scan at baseline (see outcome measures).

### Exercise safety screening

All participants will undergo medical screening by questionnaire to allow identification of those at higher risk of an adverse event during exercise. High-risk participants with known or likely occult heart disease will be excluded. Participants who choose high intensity regimes will be individually medically assessed and be stratified into categories of risk for cardiovascular events as per American College of Sports Medicine/American Heart Association (ACSM/AHA) guidelines [74]. Participants who are considered to be in a moderate-risk category who wish to participate in high-intensity exercise programmes will have a focussed medical examination, as per current ACSM guidelines.

### Choice of diet and exercise plan

If a participant is eligible and has completed all baseline assessments, they will be provided with information on each of the possible three dietary and two exercise approaches, and allowed to choose which might suit them best.

Their choice of dietary approaches will be:*Mediterranean* – High amounts of fruit, vegetables and wholegrain cereals, moderate amounts of protein (particularly from fish), nuts (up to 30 g per day), olive oil and dairy foods, and limited amounts of processed and sugary foods. Calorie counting will not be required (unless randomised to MyFitnessPal), but energy intake should be reduced by appropriate levels through promotion of appropriate foods and serving sizes.*Modified paleolithic* – Strict paleolithic diets remove all processed and cereal-based foods, legumes and dairy products which we believe is not sustainable for most overweight people long-term. Participants who choose this diet can decide to remove these foods; but we will also suggest they follow an 80:20 rule where up to one serving of dairy products, legumes and appropriate low glycaemic index, wholegrain carbohydrates are allowed each day. We believe this still fits the paleolithic philosophy while promoting greater long-term adherence through flexibility. Calorie counting will not be required (unless randomised to MyFitnessPal), but energy intake should be reduced by appropriate levels through promotion of appropriate foods and serving sizes.*Intermittent fasting (5:2 plan)* – Participants choose two days per week (any days, not consecutive, can vary from week to week to fit lifestyle) where energy intake cannot exceed 2 (females) – 2.5 (males) MJ. In practice, this usually means a small breakfast (e.g. plain porridge), no or limited food during the day, and non-starchy vegetables only for the evening meal, although other variations are possible. Participants can eat *ad libitum* on the remaining days.

The choice of exercise approaches will be from:*Current New Zealand guidelines* – recommend that participants engage in “at least 30 minutes of moderate intensity physical activity on most if not all days of the week. If possible, add some vigorous exercise for extra health benefit and fitness” (http://www.health.govt.nz/our-work/preventative-health-wellness/physical-activity). Standard printed resources available from the Ministry of Health will be used for counselling with this group. Typical recommended activities include walking briskly, exercise classes, and gardening but no mention is made of HIIT type activities (brief sessions of very high intensity exercise).*Home-based high-intensity interval training (HIIT)* – Those choosing HIIT attend a private 1-hour training session which includes focused medical evaluation and HIIT training (cycle ergometer) using rating of perceived exertion in combination with heart rate monitoring. This typically includes 3 intervals of durations of up to 30 seconds, including two maximal sprint intervals. Fitness is likely to vary amongst participants at baseline, so clinical judgment is required to adapt the initial training of participants who have low baseline cardiorespiratory fitness or other significant issues influencing exercise tolerance. However, it is intended that all participants experience at least one observed interval that achieves 80-90 % of their estimated maximum heart rate which allows the participant to recognise the required intensity, and for further identification of any undisclosed cardiac symptoms. Participants then use heart rate monitors to record unsupervised HIIT sessions for another week, ensuring further confirmation that the required intensity is being achieved. Training and resources are then provided outlining how HIIT can be achieved at home. Four different protocols are provided including a “beginners” HIIT protocol (e.g. 10 second intervals at 90 % intensity repeated 3–5 times), and then three harder options. These include maximal (90 % maximum heart rate) and submaximal (80 %) options, involve a variety of interval lengths (e.g. 30 seconds to 4 minutes), and number of repeats (3–10 times) [70, 72, 75, 76]. In general, participants will be encouraged to gradually increase their HIIT from a beginners level to ultimately being able to complete three approximately 15-minute (allowing for warm-up and cool-down) sessions of HIIT each week following one of the submaximal or maximal options. A variety of possible exercises are suggested including sprinting, stair climbing, exercise equipment such as exercycles or rowing machines, and activities such as star jumps, burpees and the like, as long as it is “exercise that uses most of your body and is very hard to do within seconds”. Partictipants could also choose to do high intensity sports sessions that involved sprint intervals, or use commercial gym-based HIIT classes as acceptable alternatives.

An additional resource will be provided to all participants which focuses on evidence-based behavioural weight loss strategies known to be successful, including stimulus control, problem solving, stress reduction and dealing with negative thinking [77].

### Randomisation

Once participants have chosen their diet and exercise approach, randomisation will occur using sequentially numbered opaque sealed envelopes prepared by the statistician. The participants will be stratified by sex and random length blocks will be used to allocate the treatment. Participants will then be booked into their first intervention session.

### Intervention groups and sessions

*Control* – those randomised to the control condition will meet with research staff to discuss which diet and exercise options would suit them best. They will also receive the resource detailing the evidence-based behavioural weight loss strategies noted above. They will then be left to their own devices for the remainder of the study (except for attending all outcome assessments).*Regular brief support* – Participants in this group will attend an appointment at the study clinic once a month to be weighed. During this time they will have the opportunity for a 5–10 minute conversation with research staff to assess progress, review and brainstorm solutions to problems if any exist, and encourage adherence. These sessions are modelled on our successful *HEAT* study and provide an opportunity for support and ongoing assistance with strategies [22].*App* – Participants in the app group will attend an appointment to learn how to use MyFitnessPal to monitor their energy and macronutrient intakes. They will be provided with assistance in setting up their MyFitnessPal account to be compatible with their chosen diet, and will be shown how to use the app on their smartphone and/or computer. Participants will be asked to monitor their dietary intake every day for the first month, and for one week of every month for months 2–12.*Daily self-weighing* – Individuals randomised to this group will receive instruction and support about weighing themselves every day (same time of day and degree of clothing). Participants will text their weight or enter it online using a web page connected to our secure database each day which will have a graphical display. Progress and adherence to entering/sending weight data will be checked every week and reminder texts sent where necessary. Every month, research staff will provide personalised progress feedback and support by email.*Biochemical hunger training* – This group will follow a 4-week protocol that trains them to recognise “real” (biochemical) hunger by associating feelings of hunger with blood glucose levels following fingerprick testing with portable glucometers. Our protocol is based on that of Ciampolini et al. [45] but adapted slightly following piloting. In the original method, participants are only able to eat if blood glucose is less than 4.7 mmol/L [45]. Our pilot testing showed that use of an individualised blood glucose cut-off (average of fasting blood glucose over two days) rather than 4.7 mmol/L improved adherence to testing and reduced eating when blood glucose was not below the cut-off [78]. Before every desired eating occasion, participants will be instructed to note their intensity of hunger on a 100mm visual analogue scale and their measured blood glucose. If their blood glucose is higher than their personal cut-off, they are advised to engage in some other activity as a distraction and wait at least one hour. At this time, they assess their feelings of hunger again and repeat the measurement if they still want to eat, until their blood glucose is under their individualised cut-off. Over time, participants learn to relate physical feelings of hunger with their blood glucose and to eat only when physically hungry. Participants will be advised to follow this procedure for two weeks. In weeks 3 and 4, the blood glucose testing is optional, but all other recording (intensity and type of hunger, and resulting food intake) continues. Participants will be in regular contact with support staff, who will advise them how to proceed, answer any queries and provide encouragement. In months 2–12, participants will be advised to repeat the recording process (with or without fingerprick blood glucose testing) for one week of every month.

### Outcome assessments

Outcome assessments will occur at 0 (baseline), 6 (mid-point of intervention), 12 (end of intervention) and 24 (end of follow-up) months as shown in Table 1. Adherence measures are more frequent as outlined elsewhere.

**Table 1 Tab1:** Timing of outcome assessments in the SWIFT study^*^

Outcome	Month			
	0^†^	6	12	24
Height	x			
Weight^§^	x	x	x	x
Bioimpedance	x	x	x	x
DXA scan	x		x	
Blood pressure	x	x	x	x
Blood samples	x		x	x
3-day diet record	x	x	x	x
Accelerometry	x	x	x	x
Aerobic fitness	x	x	x	x
Questionnaires	x	x	x	x
Demographics	x			
Personality	x			
Resilience	x			
Dieting and weight history	x			
Intuitive eating	x	x	x	x
Dutch eating behaviour questionnaire	x	x	x	x
Depression, anxiety, stress	x		x	x
Disordered eating	x		x	x
Self-monitoring	x	x	x	x
Self-efficacy	x	x	x	x
Satisfaction with diet and exercise		x	x	x

^*^Two visits are required at each time point in order to complete all measurements

^†^0 refers to baseline

^§^More frequent weights will be available for those in the regular brief support and daily self-weighing groups but these are for adherence measures rather than outcomes

#### Anthropometry and body composition

All measures (except DXA) will be obtained in duplicate by trained assessors blinded to support group allocation. If duplicate measures differ by more than 1 %, a third measurement is obtained and the median is used as the final value. Height will be measured by fixed stadiometer (Heightronic, QuickMedical, WA, USA) and weight by electronic scales (Tanita BC-418) with participants wearing light clothing and no shoes. Waist circumference will be measured at the narrowest point between the lower costal border and the top of the iliac crest by non-elastic tape. Body composition will be measured by segmental Bioelectric Impedance Analysis (BIA, Tanita BC-418) at each time point and by dual energy x-ray absorptiometry (Lunar Prodigy) at 0 and 12 months only. Measures of systolic and diastolic blood pressure will be obtained using an automated sphygmomanometer (Omron Model HEM-907).

#### Blood tests

Blood samples will be collected from participants by a registered nurse following a 12-hour overnight fast. High-sensitivity CRP will be measured using a CRP Unimate kit from Roche Diagnostics on a Cobas Mira Plus Analyzer (Roche), Interleukin-6 by using Quantikine ELISA Kits (R&D Systems) following the instructions provided by the manufacturer, adiponectin by radioimmunoassay (Linco Research, St Charles, MO, USA), ghrelin (active) by immunoassay (Human Gut Hormone Panel LINCOplex Kit, LINCO Research, St. Charles, MO, USA), and plasma total cholesterol (TC), HDL cholesterol (HDL-C), and TG concentrations by enzymatic methods using a Cobas Mira Plus Analyzer. LDL cholesterol (LDL-C) will be calculated using the Friedewald formula [79].

#### Diet, physical activity and fitness

Participants will complete a weighed 3-day diet record (one weekend day, two week days) with energy and nutrient intakes calculated using Kai-culator (University of Otago, 2011). Physical activity (counts per minute and intensity categories) and sleep duration and timing (minutes, bed time, wake time) will be measured using ActiGraph accelerometers (GT3X, ActiGraph, Pensacola, FL) worn around the waist over 7 days. Participants wear the accelerometers for the full 24-hour periods, which provides both sleep and activity data and lowers the chance of missing data from participants not remembering to reattach the accelerometer straight after waking. Aerobic fitness will be evaluated by estimating participants’ VO^2^max, using the YMCA submaximal cycle ergometer test [80].

#### Questionnaires

Demographic information (age, sex, education, ethnicity, employment, income, household structure) will be obtained at baseline using the relevant New Zealand census questions (http://www.stats.govt.nz/Census). Other questionnaires to be completed at baseline only include the Ten-item personality inventory [81] which gives broad scores for the ‘Big Five’ personality dimensions, the Brief Resilience scale [82] which assesses the ability to bounce back or recover from stress, and the Dieting and weight history questionnaire [83]. Questionnaires completed at baseline, and repeated at 6, 12 and 24 months (not all measures at all time points) will include the Intuitive Eating scale [84] which measures the tendency to follow hunger and satiety cues when eating, the Dutch Eating Behavior questionnaire [85] which evaluates dietary restraint and emotional and external eating, the Depression Anxiety Stress scale (DASS21) [86], a well-accepted short measure of depression, anxiety and stress, the Disordered Eating questionnaire EDE-Q [87] investigating restraint and concerns about eating, shape and weight, a self-monitoring questionnaire [39], assessing how often they weigh themselves and track their eating and physical activity, selected questions on perceived benefits, self-efficacy and enjoyment of physical activity, self-efficacy for health eating and behavioural skills used for weight management [88] and satisfaction with the dietary and exercise approaches chosen.

#### Adherence

Adherence to support strategies will be assessed as follows:

Brief support: attendance at monthly sessions.

App use: frequency, consistency, and comprehensiveness of food recording during first month (daily) and for one week every month for months 2–11 inclusive.

Daily-self weighing: by the number of daily weights recorded in the database.

Hunger training: analysis of the 4-week booklets in month 1 and the weekly recordings for months 2–12 the percentage of times participants measured their glucose before eating, and only ate if blood glucose was lower than the personal cut-off.

Adherence to the dietary regimes will be measured using the 3-day diet records. Those choosing to follow intermittent fasting will complete a 4-day diet record at 6, 12 and 24 months to allow collection of two fasting and two non-fasting days. Adherence to the exercise regime will be measured by the accelerometers. In addition, HIIT participants will wear a Polar RC3 GPS heart rate monitor during all home HIIT sessions for a one-week period at baseline, 3, 6, 9 and 12 months to evaluate intensity attained during the sessions.

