Strong social support is considered an important adjunct to successful weight loss or maintenance [20]. The use of personalised support with nutrition and activity specialists is known to be effective [21], however it is expensive and rarely accessed. Alternative forms of low-intensity but regular support, delivered by non-specialists can result in similar benefits, at a fraction of the cost [22]. Brief monthly support, such as is found in many commercial weight loss programmes, also appears to maintain weight loss better over 2–3 years than other forms of support including interactive websites and self-directed control [23]. However, because such support cannot continue indefinitely, and ongoing development of innovative technology, determining the efficacy of other, low-cost strategies is currently of great interest [24].

Self-monitoring of weight, food intake and/or activity levels has been shown to be one of the most effective strategies employed for successful weight management [25]. However, monitoring of food and activity is time-consuming and adherence dramatically declines over time [26]. The advent of mobile “apps” may offer a more effective way of monitoring food/ activity patterns due to instant feedback of a wealth of information [27]. While self-monitoring strategies are a common component of the myriad of commercially available apps [24], whether they are effective at encouraging behaviour change has rarely been examined, despite their widespread use [28]. Although the top five self-monitoring apps each have a user base of more than 10 million people [28], only one appears to have been tested in a clinical trial [29]. Laing et al. [29] recently demonstrated that use of MyFitnessPal alone, with no accompanying dietary or exercise advice, did not produce significant weight change over 6 months in comparison with usual care. The apparent lack of effect may be due in part to the sharp declines in adherence to app use after the first month [29]. Perhaps this is not surprising given that the response of individuals to self-monitoring can vary considerably, ranging from the “well-disciplined” who endorse this approach, to those that have “diminished support”, where other co-existing factors take precedence [30].

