### Aims and objectives

The goal of our study is to determine whether allowing participants to choose from a selection of appropriate diet and exercise plans, within the context of a randomised controlled trial evaluating four different support strategies, enhances adherence and promotes greater weight loss and positive health outcomes. Giving people the choice of which diet and exercise regime is best incorporated into their particular lifestyle is expected to improve adherence, reflects real-world conditions, and is consistent with the lack of evidence for meaningful differences between diet modalities. Acknowledging this concept in conjunction with testing different support strategies offers a unique opportunity to determine how best to support individuals to make dietary and exercise changes under real-world conditions.

The primary aim of our study is to determine the effectiveness of different support strategies (control condition, brief support, daily self-weighing, app use, hunger training) on weight loss at 12 and 24 months. Secondary aims are to determine:(i)the effect of different support strategies on body composition, dietary intake, exercise, inflammatory markers, blood lipids and lipoproteins, adiponectin, ghrelin, and psychosocial indices at 12 and 24 months(ii)the degree of adherence to each of the support strategies over the 24 months(iii)the degree of adherence to each of the diet (Mediterranean, intermittent fasting, modified Paleo) and exercise (current recommendations, HIIT) plans that are selected over the 24 months and the outcomes within these self-selected groups.

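### Hunger-training adherence has no scheduled denominator, so unrecorded periods do not lower it, whereas stopping lowers the adherence measure in the other three strategies

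*Protocol article*

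**What the plan says.** Secondary aim (ii), under Aims and objectives in the protocol article, is to determine "the degree of adherence to each of the support strategies over the 24 months". The Adherence section gives one rule per strategy:

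- "Brief support: attendance at monthly sessions".
- App use: how often, how consistently and how fully food was recorded, over stated recording periods.
- Self-weighing: "by the number of daily weights recorded in the database".
- For the hunger-training arm, the sources are given as "analysis of the 4-week booklets in month 1 and the weekly recordings for months 2–12", and the score drawn from them is "the percentage of times participants measured their glucose before eating, and only ate if blood glucose was lower than the personal cut-off".

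The section on intervention groups and sessions sets the hunger-training recording schedule: four weeks in month 1, then one week a month in months 2 to 12. It asks for glucose testing in the first two weeks and makes it optional after that.

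**The concern.** The first three measures fall when a participant gives up: a missed session, a missing weight or an unlogged day each counts against them. The hunger-training measure is different in kind. Eating occasions are known only from the participant's own records, so those records supply both the numerator and the denominator. A participant who stops recording adds nothing to either.

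Aim (ii) invites the reader to set the four strategies side by side, and adherence is central to the trial's rationale. The Background itself warns that "monitoring of food and activity is time-consuming and adherence dramatically declines over time". If that holds here, the hunger-training figure would describe the periods in which people were still engaged, while the other figures would reflect disengagement too.

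**Working it through.** The protocol article states no adherence figure, so there is nothing to reproduce. The check compares how each definition responds when a participant stops.

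**Inputs.** From the recording schedule: 4 + 11 = 15 scheduled weeks, or 15 × 7 = 105 days. Assumed: 12 monthly sessions and 365 possible daily weights over the 12-month intervention, and an equal number of eating occasions, *k*, on each day.

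**Definition.** Let *d* be the number of days recorded and *p* the share of recorded occasions that meet the glucose rule.

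- As written: score = *pkd* / *kd* = *p* for any *d* > 0. It does not depend on *d*, and for *d* = 0 it is 0/0.
- On a scheduled denominator: score = *pd* / 105.

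**One participant who stops everything after month 1 (*d* = 28).**

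| Measure | Result |
|---|---|
| Hunger training as written, assumed *p* = 60 / 80 / 90 % | 60 / 80 / 90 % |
| Hunger training as written, months 2–12 alone | 0/0, drops out |
| Hunger training on scheduled days, *p* × 28/105 | 16 / 21 / 24 % |
| Brief support, 1/12 | 8 % |
| Self-weighing, 28/365 | 8 % |

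**Arm level, illustration only.** Assume 75 % compliance among those still active, and 20 % to 50 % who stop so early that they contribute almost nothing.

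- Stoppers counted as zero: 0.80 × 75 = 60 %; 0.50 × 75 = 37.5 %.
- Recorders only: 75 % in both cases.
- Gap: 75 − 60 = 15 points; 75 − 37.5 = 37.5 points.

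**A pull in the other direction.** Testing is asked for on 14 of the 105 days and is optional on the other 91. If an untested occasion counts as a failure, a participant who records all 105 days but tests only on the first 14 can score at most 14/105 = 13 %. One who follows the rule perfectly for those 14 days and then stops recording scores 14/14 = 100 %. The score can therefore fall with persistence. For the same reason, its level relative to the other strategies could be biased either way.

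**The case against.** **The denominator is inferred.** The article never says that the percentage is of recorded occasions. The sentence lacks a connecting word and could be read as covering booklet completion as well as the glucose rule. This is a condensed article, and the full protocol may count unreturned booklets as non-adherent. That stands as a caution. But the article does fix a rule for each strategy, it names no other source of eating occasions, and followed as written it gives a conditional figure.

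**The footing of the other arms is partly assumed.** No analysis population is given for any adherence measure, so it should not be said that the other figures cover everyone randomised. What can be said is that those measures fall when a participant stops.

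**Two stronger readings are tempting.** A reader might infer that hunger training will look better adhered to by 15 to 38 points. The document does not support this: compliance and stopping rates are assumed, self-weighing is defined as a count and not a percentage, and optional testing acts on the same score in the opposite direction. The Background remark about declining adherence concerns food and activity monitoring in general, so it does not show how many would stop hunger training.

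A reader might also infer that high-intensity interval training has the same flaw, because the heart-rate monitor sees only sessions that take place. It does not. Adherence to the exercise plans is measured by accelerometer, scheduled for all participants at each assessment. The monitor is an addition "to evaluate intensity attained during the sessions". Three sessions a week is a level to be reached eventually, so it is not a denominator from the start.

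**The consequence is limited.** No test of adherence between support strategies is stated, and the planned cohort analysis concerns adherence to the diet and exercise approaches. This stands.

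**Conclusion.** The point holds in a limited form. As published, the hunger-training measure does not register stopping, while the brief-support, self-weighing and app measures do. The figure reported for aim (ii) would describe recorded periods only and could not be read alongside the other three. This rests on the reading that eating occasions come solely from the participant's booklets and weekly recordings, which are the only sources the article names.

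The effect on one participant's score can be large: under the stated assumptions, 80 % as written against 21 % on scheduled days. The 15 to 38 points at arm level illustrate the mechanism and do not estimate a bias. Neither the size nor the net direction of any distortion between strategies can be derived from the document. The primary comparison of weight is not touched.

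**What to change.** In the adherence section and the analysis plan, define hunger-training adherence in two steps:

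1. For all participants randomised to hunger training, the proportion of the 15 scheduled recording weeks (4 in month 1, then one a month in months 2 to 12) with a returned record, counting unreturned weeks as zero. The participant in the example above who stops after month 1 would score 4/15 = 27 %.
2. The glucose-rule percentage, labelled as conditional on a returned record and shown with the number of participants and weeks that contribute.

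The optional testing after week 2 and the scoring of testing up to month 12 should be reconciled at the same time, so that the second figure has a clear meaning.

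The cost is a change of wording. The schedule is already set and the records are already to be collected. The downside is that the headline hunger-training adherence may be lower.
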